### 1.2 Locations and time frame

Department of Nephrology

Herlev Hospital

[name]

[name]

Denmark

Study initiation is expected in Spring 2010 and completion by 1.3.2012. The study is complete when the last patient has completed the last visit. Recruitment rate is expected to be 1/week.

### 1.3 Collaborators

The GCP unit Copenhagen University

Bispebjerg Hospital, [name]

[name]

[name]

The study protocol and information material will be submitted for approval by the Danish Medicines Agency and the regional ethics committee for Region Hovedstaden. The study will be submitted to the [www.clinicaltrials.gov](http://www.clinicaltrials.gov) database before inclusion of the first participant.

## Background

The number of patients on chronic dialysis is increasing in Denmark and the rest of the Western part of the world (1;2). This is partly due to the fact that dialysis treatment is now also offered to patients with concomitant serious diseases. The prevalence as well as the incidence of end stage renal disease (ESRD) has been increasing in the past many years even if it seems that the incidence has been stabilised in the past 3 years in Denmark (2). It is only a limited part of patients with chronic kidney failure who are offered renal replacement therapy in the form of kidney transplants.

Patients with chronic kidney disease (CKD) have increased cardiovascular morbidity and mortality mainly due to arteriosclerosis even at young age. Therefore survival amongst patients on chronic dialysis is lower than for the normal population. It is essential to improve treatment for these patients in attempts to hinder or slow down progression of CKD to ESRD.

Almost all patients with CKD also suffer from moderate to severe hypertension. Treatment of hypertension is one of the cornerstones in treatment of CKD and hindrance of disease progression as well as reducing cardiovascular (CV) disease risk. It has been shown that the renin-angiotensin-aldosterone system (RAAS) plays a central role in progression of uraemia. Antihypertensive treatment that blocks the RAAS has specific renoprotective properties, independent of blood pressure (BP) reduction (3;4). The use of Angiotensin Converting Enzyme inhibitors (ACEi) and Angiotensin-2-receptorblockers (ARB) is nowadays standard in the treatment of CKD. Several studies have shown beneficial effect on CV morbidity and mortality in groups of patients with heart failure (5), hypertension (6), diabetic nephropathy (7) and non-diabetic nephropathy with proteinuria (8).

Furthermore there are studies who investigate an even more intense blockade of the RAAS, namely including an aldosterone inhibitor. There are studies showing a beneficial effect on survival of patients with heart failure (9;10). Furthermore triple blockade (ACEi, ARB and aldosterone inhibitor (spironolactone)) has an additive effect in reducing proteinuria, a surrogate marker of kidney function and disease progression, in patients with non-diabetic kidney disease (11;12).

It is proposed, that progression of renal insufficiency is multifactorial. Amongst these factors are vasoactive hormones, growth factors and cytokines (13). Besides the so-called classic (genomic) effects of aldosterone on fluid and potassium homeostasis, aldosterone also has non-genomic effects. Animal studies have suggested aldosterone to play a role in the development in hypertensive and arteriosclerotic disease in the heart and blood vessels (13;14).

Discussions whether it is the classical or non-classical effects of aldosterone that are responsible for these deleterious effects are still ongoing (15).

In patients with CKD another vessel disease is also present – the uraemic intima media stiffness. It differs in appearance from atherosclerosis in its universal form in both arteries and arterioles (16).

The vessels gradually change from elastic to very rigid formations increasing the overall load on the vessels. Arterial stiffness is an independent predictor for CV morbidity and mortality in the background population as well as in patients with CKD (17;18) and a reduction in the pulse wave velocity (PWV) can reduce morbidity and mortality in this group of patients (18).

In hypertensive patients with a serum creatinine < 300 µmol/L a positive and independent correlation between s-creatinine and aortic PWV has been found (19). Age, blood pressure and diabetes mellitus (DM) are other factors that independently influence PWV. A population study showed that PWV as well as the Augmentation Index (AIx) change with age. PWV is relatively constant up till the 8^th^ decade after which it tends to increase, whereas AIx rises through the first five decades after which it is relatively constant (20). Changes in the central and peripheral pulse wave parameters reflect changes in the vascular structure and function, which provide good evidence of changes in arterial stiffness. Several studies have been performed using the applanation tonometry method, where ACEi as well as ARBs have been found to reduce arterial stiffness (21;22). Treatment with ACEis and/or ARBs in CKD has been shown to be beneficial (23;24). When pulse wave measurements have been performed, AIx and other relevant values are derived, as well as the PWV.

Arterial stiffness is also depicted in the well known 24 hour ambulatory blood pressure measurement (AMBP). A quantitative measure for the stiffness is the Ambulatory Arterial Stiffness Index (AASI), derived from these measurements (25-30). AASI has been shown to be an independent predictor for stroke in the background population (27-29;31) and may be useful as a surrogate parameter for assessing the risk of CV disease (31). This has not been investigated for CKD.

The investigators of this study are currently examining the relationship between arterial stiffness as measured by applanation tonometry and the correlation to AASI in CKD stages 2-5 (ALBLOCK-1).

Results of combination therapy, in the form of dual blockade of the RAAS by ACEi and ARB, points towards a beneficial, additive effect on arterial stiffness in different patient populations. Studies to explore the effect of aldosterone inhibition on arterial stiffness assessed by applanation tonometry in patients with CKD have previously not been performed. A possible positive effect could bring this treatment modality into the awareness of doctors treating patients with CKD in an attempt to attenuate their overt risk of CV morbidity and mortality.

Arterial stiffness has been shown to be a modifiable factor during different treatment regimens in patients with essential hypertension(32-38). It has not been studied in CKD.

In this protocol – ALBLOCK-2 - intervention is the relatively new aldosterone receptor antagonist eplerenone. Eplerenone has fewer side effects than spironolactone, the previously single aldosterone blocker on the market. Prescription indications are at present heart failure after acute myocardial infarction or potassium sparing diuretic. It is known that aldosterone inhibition using spironolactone reduces albumin excretion in diabetic and in non-diabetic CKD(39). Besides this expected effect which has been studied in a very recently completed study by our group (data not published at present) eplerenone reduces stiffness in the smaller resistance vessels when evaluated by electro myograph in these vessels from patients with hypertension(40).

This effect has not been studied in CKD.

## Study description

### 3.1 Aim and hypothesis

The hypothesis of the ALBLOCK-2 study is that inhibition of aldosterone receptors using eplerenone in standard dosing will lead to a reduction in arterial stiffness in patients with different stages of CKD.

The aim is to reduce PWV by treating patients with eplerenone.

Secondarily it is studied whether AASI changes.

### 3.2 Design

The study is a prospective, randomized, controlled, parallel group, phase IV study.

| Week number | -4 | 1 | 2 | 4 | 8 | 12 | 16 | 20 | 24 |
| --- | --- | --- | --- | --- | --- | --- | --- | --- | --- |
| Visit number |  | 1a/1b | 2 | 3 | 4 | 5a/5b | 6 | 7 | 8a/8b |

A BP target of 120-130/80-90 is set and investigators will strive to keep this constant in patients throughout their enrolled period. Therefore a run-in period of 4 weeks has been planned. All patients are to continue on their normal medication including blockers of RAS, which most of these patients receive before enrolment. If anti-hypertensive treatment needs to be intensified, this is done by adding beta blocker, calcium antagonist or methyldopa. If BP is lower than target pressure medication will be withdrawn, primarily via reduction in calcium antagonism or beta blockade, while RAS-blockade in the initial form is aimed to be kept as it was.

If study participants fail to tolerate the full dose of eplerenone 50 mg once daily, dose will be reduced to 25 mg once daily. In case of the patients receiving potassium supplements at time of enrolment these will be withdrawn before start of intervention.

Participants are randomized after the run-in period and are given consecutive numbers of identification.

The study plan is identical for the two groups.

### 3.3 Endpoints

Primary endpoint is the difference in PWV measured by the tonometer (Millar, Houston, Texas, USA) and using the SphygmoCor® hard- and software.

Secondary endpoints are pulse wave morphology, evaluated by the AIx, BP, subendocardial viability ration (SEVR), heart rate, time to reflection (TR), ejection duration (ED), pulse pressure (PP), kidney function (estimated glomerular filtration rate (eGFR)), p-creatinine, AASI and albuminuria.

P-potassium and p-creatinine are used for safety monitoring.

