Pulse wave measurements are performed by the same, trained observer in the morning under standardized conditions. Before performing the actual measurements, marks are made on the skin of the patient over the part of the a. radialis, a. carotis, and a. femoralis where the pulse is most prominent. The suprasternal notch (SN) is used as reference point and is also marked. A tape measure is used to measure the distances between the SN and a. radialis, carotid artery and a. femoralis, respectively. Patients are then requested to rest in the supine position, in a quiet room of constant temperature for 10 minutes. The measurements are all undertaken on the right side. Patients have to be in the fasting state and have to refrain from smoking 8 hours before examination. Diabetics are allowed a light meal and all participants are allowed a glass of water. All medications including study medication are to be taken after examination. Quality of the measurements is evaluated partly by a visually acceptable curve of the peripheral pulse wave and partly by a maximum difference between 2 successive measurements of ≤7% and an average height of the wave of > 80 mV(42). Pulse wave measurements are done in two sets. The first is the pulse wave (PW) and after this the PWV. The AIx is derived from the PW. It is calculated as the percentage of augmentation (AG) of the pulse pressure (PP). On the recordings of the peripheral waves the PP, the first peak of the pulse wave (P1) and the second peak (P2) are marked. The augmentation is the difference between P1 and P2. And the AIx is this difference taken out of the PP. These calculations are all performed automatically by the SphygmoCor software. An acceptable Quality Index (QI) is > 80%. QI is calculated by the software from the other stated quality indicators (pulse height, max. 7 % difference between two measurements).

*Ambulatory blood pressure measurements*

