| 7 | Week 20 | b-haemoglobin, b-leukocytes, b-thrombocytes, p-bilirubin, p-ALAT, p-alkaline phosphatase, hsC-reactive protein, p-creatinine, p-urea, p-sodium, p-potassium, p-bicarbonate, p-glucose, p-albumin, p-calcium-ion, p-phosphate, p-uric acid, eGFR. |  |
| 8a | Week 24 | b-haemoglobin, b-leukocytes, b-thrombocytes, p-bilirubin, p-ALAT, p-alkaline phosphatase, hsC-reactive protein, p-creatinine, p-urea, p-sodium, p-potassium, p-bicarbonate, p-glucose, p-albumin, p-calcium-ion, p-phosphate, p-uric acid, eGFR, p-cholesterol, p-triglyceride, p-HDL, P-LDL, p-parathyroid hormone (PTH) and 1,25-dihydroxy-cholecalciferol (vitamin D3), 25-OH-Vitamin D, p-renin og p-aldosterone. | 24 hour urine sampling |
| 8b | Week 24 | return of AMBP device |  |

Study participants are to collect 24 hour urine samples for analysis of concentrations and total amounts of albumin, creatinine, potassium, sodium and calculation of creatinine clearance at all three visits where pulse wave measurements are made (visits 1, 5a and 8a).

Estimated GFR (eGFR) is routinely performed using the CKD-EPI formula (51).

Re blood samples: At all samplings an amount of blood between 50 and 68 ml of blood will be drawn, depending on purpose of the visit. Analysis is routinely performed in the hospital central laboratory at Herlev Hospital except vitamin D which is performed by Capio Diagnostik and p-renin and aldosterone, which are analyzed at The Dept. of Clinical Physiology, Glostrup Hospital. Both laboratories are usual collaborators for these tests.

Re urine samples: These will be analyzed as routine tests at the central laboratory in Herlev Hospital.

Re frozen tests: Samples will be saved and frozen for later analysis.

Samples are stored in a locked -80°C freezer, which is connected to an alarm system at Herlev Hospital.

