### 3.13 Practical performance of study

Patients who fulfil the inclusion criteria and who are interested in participating in the study are informed about the study. The written information is handed out and will be thoroughly explained. A form of written informed consent is to be signed by the patient and the informant/investigator. If consent is given, dates for the study days will be given.

Demographic data will be registered.

Randomization: When inclusion criteria are met including the performance of a screening for PW measurements and the run-in period has been completed, patients are randomized to the active treatment arm with eplerenone or the control arm for 24 weeks.

Planning:

A deviation of ± 1 week from the initially planned date for visits is permitted. Collection of 24 hour urine is allowed for at time deviation of ± 3 days with respect to blood sampling. Participants’ visits are planned to be identical in both groups.

Visits are planned as shown below:

| ***Visit number*** | ***Time with reference to inclusion for the individual patient*** | ***Purpose of visit*** | ***Estimated time used for the visit*** |
| --- | --- | --- | --- |
|  | Screening | signing of written informed consent, PW measurement test, ECG, blood sampling, demographic data noted | 1-1½ hours |
| 1a | Week 1 | randomization, PW measurement, AMBP, blood sampling, 24 h urine, study medication handed out | 1 hour |
| 1b | Week 1 | return of AMBP device | 10 minutes |
| 2 | Week 2 | blood sampling, BP, increase in study medication | 30 minutes |
| 3 | Week 4 | blood sampling, BP, study medication handed out | 30 minutes |
| 4 | Week 8 | blood sampling, BP, study medication handed out | 30 minutes |
| 5a | Week 12 | PW measurement, AMBP, blood sampling, 24 h urine, study medication handed out | 1 hour |
| 5b | Week 12 | return of AMBP device | 10 minutes |
| 6 | Week 16 | blood sampling, BP, study medication handed out | 30 minutes |
| 7 | Week 20 | blood sampling, BP, study medication handed out | 30 minutes |
| 8a | Week 24 | PW measurement, AMBP, blood sampling, 24 h urine, study medication and packages returned | 1-1½ hours |
| 8b | Week 24 | return of AMBP device | 10 minutes |

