**n = 36.3058**

delta = 1

sd = 1.5

sig.level = 0.05

power = 0.8

alternative = two.sided

NOTE: n is number in *each* group

Patients who are with drawn are not replaced.

Differences in PWV will be statistically examined using paired t tests.

The secondary effect parameters will also be examined using this statistic method. For the groups as a whole two sample t test will be applied. If data do not fit the normal distribution they will be transformed.

1. ***Quality control***

Normal procedures for quality control will be followed, see ICH GCP Guidelines. Data will be monitored by The GCP unit at Copenhagen University Hospital, Bispebjerg Hospital, [name], [name], [name]. As informed consent is given, a permission from the participant for the Danish Medicines Agency and the GCP unit to have access to the patient’s hospital medical files will be sought. A copy of the text is available (in Danish).

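### The primary endpoint names no visit, although PWV is measured after baseline at both week 12 and week 24, and the arterial segment is only implied

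*Protocol*

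**What the plan says.** - Endpoint (section 3.3): "Primary endpoint is the difference in PWV measured by the tonometer (Millar, Houston, Texas, USA". No visit or arterial segment is given, nor whether the difference is between groups or from baseline.
- Aim (section 3.1): "The aim is to reduce PWV by treating patients with eplerenone". Again there is no time point.
- Schedule (section 3.11): urine is collected "at all three visits where pulse wave measurements are made (visits 1, 5a and 8a"). The visit table in section 3.13 puts visit 1a at week 1, 5a at week 12 ("PW measurement, AMBP, blood sampling, 24 h urine, study medication handed out") and 8a at week 24 ("PW measurement, AMBP, blood sampling, 24 h urine, study medication and packages returned"). Two measurements therefore follow baseline.
- Method (section 3.4): "A tape measure is used to measure the distances between the SN and a. radialis, carotid artery and a. femoralis, respectively". The path over which PWV is calculated is not named.
- Sample size (Statistics): a relevant difference of 1 m/s and an SD of 1.5, both simply for PWV; two-sample t test, two-sided 0.05, power 0.8, 37 per group needed and 40 planned.
- Analysis (Statistics): "Differences in PWV will be statistically examined using paired t tests". A two-sample t test is then mentioned for the groups as a whole. Neither test is tied to a visit.

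**The concern.** The time point is part of what a primary endpoint is. Section 3.3 undertakes to define the endpoint and leaves that part out, so this is not detail that can wait for a statistical analysis plan. With two post-baseline measurements of equal standing, a significant result at week 12 with a null result at week 24, or the reverse, has no agreed reading.

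Two features of the design make the gap matter more:

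- The control group continues usual therapy and no placebo is described, so fixing the comparison in advance is an important protection against choosing the more favourable visit.
- Withdrawn patients are not replaced, and the margin over the required number is only 40 − 37 = 3 per group. The week 12 and week 24 samples may therefore differ.

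The analysis sentence does not close the gap. A paired t test compares a patient with himself or herself over time. It does not compare eplerenone with control, which is what the two-sample sample size was calculated for.

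**Working it through.** **1. Reproduce the plan's figure.** Inputs from the Statistics section: difference 1, SD 1.5, two-sided alpha 0.05, power 0.80.

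- Normal approximation: n = 2 × [1.5 × (1.960 + 0.842) / 1]² = 35.3.
- Exact two-sample t test (noncentral t): n = 36.306, rounded up to 37. The protocol prints 36.3058.
- Power is 80.8% at 37 per group and 83.8% at 40.

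The figure is right, and it is for one comparison at 0.05.

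**2. Count the candidate comparisons.** Post-baseline PWV visits are 5a (week 12) and 8a (week 24). Between-group tests of PWV that fit section 3.3: two.

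**3. False positive risk if either visit could count.** For two test statistics Z1 and Z2, each standard normal under the null with correlation r:

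risk = 1 − P(|Z1| ≤ 1.96 and |Z2| ≤ 1.96)

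| r (assumed) | risk |
| --- | --- |
| 0 (independent) | 1 − 0.95² = 0.0975 |
| 0.5 | 0.091 |
| 0.7 | 0.083 |
| 0.8 | 0.078 |
| 0.9 | 0.070 |

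The protocol gives no correlations, so r is an assumption. For tests of PWV level, r is the correlation between the two visits. For tests of change from a shared baseline, with equal correlation c among all three visits, the covariance of the two changes is 1 − c and each variance is 2(1 − c), so r = 0.5. Over the range 0.5 to 0.8 the risk is 0.078 to 0.091.

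**4. Cost of keeping both visits as co-equal primary tests.** With Bonferroni at 0.025 each, the exact calculation gives n = 44.05, so 45 per group. Power at 40 per group falls to 75.5%. Naming one visit avoids this.

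**5. Effect of adjusting for baseline PWV.** Suppose 1.5 is the SD of a single PWV level and b is the correlation between week 1 and week 24. The residual SD is then 1.5 × √(1 − b²). With 40 per group and 77 degrees of freedom:

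| b (assumed) | residual SD | power for 1 m/s |
| --- | --- | --- |
| no adjustment | 1.50 | 83.8% |
| 0.5 | 1.5 × √0.75 = 1.30 | 92.5% |
| 0.8 | 1.5 × √0.36 = 0.90 | 99.8% |

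If 1.5 is instead the SD of a change, the ANCOVA residual SD cannot exceed 1.5. Power then stays at about 84% or better, apart from one degree of freedom.

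**The case against.** The strongest reply is that the intended endpoint is easy to guess. Patients are randomised to 24 weeks of eplerenone or control and the last pulse wave measurement is at week 24, so week 24 is the natural reading. The 1 m/s difference rests on reference 19, whose listed title concerns aortic PWV, and the Background cites the same reference for aortic PWV. Both hints are fair. They show that the repair should be uncontroversial, but neither is tied to the endpoint in section 3.3.

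A second reply is that the protocol nowhere says a positive result at either visit would count as success, and that the plural in the analysis sentence may be loose wording. This stands. The 8 to 9% is the risk under a rule the protocol leaves open, not one it adopts.

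A reader might also infer from the three measured distances that carotid-radial and carotid-femoral PWV are both candidates, which would double the comparisons. The protocol does not support that. It never says a carotid-radial PWV is calculated or tested, and section 3.4 gives the radial site its own use in pulse wave analysis and central pressure. The segment is under-stated, but a second primary segment is not shown to exist, so no error rate is attached to it.

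Nor do the documents show that anyone would compare the groups as results accrue. Section 3.10 says only that data are entered continuously, and no interim comparison is described.

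**Conclusion.** The point holds for the visit: the primary endpoint has no time point, and two post-baseline measurements fit its definition. For the segment the fault is smaller, because it is implied rather than stated.

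The sample size arithmetic is correct for one comparison. What is missing is a statement of which comparison that is. The worst-case false positive risk is about 8 to 9% instead of 5%, assuming a correlation of 0.5 to 0.8 between the two tests and a reading in which either visit may count. It would be wrong to conclude that the trial's error rate is that high as planned: with week 24 fixed in advance, 0.05 applies unchanged. The point should be corrected because it bears on how the main result can be read, and the correction is small.

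**What to change.** Two passages need editing together.

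- **Section 3.3.** State that the primary endpoint is carotid-femoral (aortic) PWV at visit 8a (week 24), compared between eplerenone and control. Name PWV at visit 5a (week 12) as supportive.
- **Statistics.** For the primary endpoint, replace the paired t tests with a between-group ANCOVA of week 24 PWV, adjusted for the visit 1a value. State whether the SD of 1.5 refers to a level or a change, and to which segment.

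Naming the visit and segment closes the gap. The ANCOVA goes a step further: it makes the test match the between-group question and uses a baseline measurement already planned. If 1.5 is the SD of a level, power at 40 per group would rise from 84% to between 92.5% and over 99%, for an assumed baseline correlation of 0.5 to 0.8.

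No new measurement and no change in sample size are needed. The cost is a short edit in two sections, made before the first randomisation, and giving up the option of claiming a week-12-only effect as the primary result.
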